#### 5.4 Data Collection and Management

Baseline demographic, anthropometric, and health history data, as well as information pertaining to feeding practices and health-seeking behaviours, will be collected by field researchers employed by the KHRC. All blood samples will be collected by qualified individuals, trained specifically in pediatric phlebotomy techniques.

Visual Basic will be used to manage data. All data obtained in the field will be entered by the end of the next day. The systems used will have extensive range and checking facilities. Possible errors will be verified with field or hospital staff on a daily basis. Data collection and supplement allocation will be rigorously controlled with the help of computer monitoring. For all outcomes, a double-data entry will be used to detect errors. Flow of information, distribution of supplements, and collection of samples between households and villages and the central office at the Kintampo Health Research Centre will be ensured by supervisors on motorbikes on the same day.

#### 5.5 Data Analysis

All variables will be first explored and summarized using descriptive statistics such as number of events in person-time, incidence rates, means and standard deviations, medians and ranges, counts and proportions, and various graphs, as appropriate.

##### Primary analysis

The primary outcome, incidence of malaria, will be compared between the two groups using Poisson regression. A 95% confidence interval for the ratio between the incidence in the iron group and the incidence in the placebo group will be calculated. The upper boundary of this confidence interval will be compared to the 10% tolerance limit. If it is lower, then non-inferiority can be concluded.

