We hypothesize that the incidence of malaria will be significantly higher in children receiving iron versus a placebo of micronutrients without iron. It was decided not to use the change in anemia status as a primary outcome since, in all previous studies with powdered mineral and vitamin fortificants, anemia rates declined compared to placebo controls, or were no different from the improvement in anemia rates observed with iron drops.

Based on the 2006 estimate of “cases and deaths from fevers suspected of being malaria” for children under 5 years of age in all of Ghana (53), the baseline rate of 3.44 episodes/child/year was assumed. We estimated that a total of 351 person-years would be required to detect a 15% increase in malaria incidence rates with 80% power and at a 5% type I error. Based on the experience and expertise of the PI and co-investigator, a difference of 15% in malaria incidence was considered to be clinically significant. Knowing that all children enrolled in the trial will begin the 5-month intervention period at a similar risk level, and accounting for 15% loss to follow-up, as well as the need to test the hypothesis twice (due to the interim analysis by the Data Safety and Monitoring committee), the sample size has been calculated as 1940 children per seasonal cohort (970 per group), or a total of 3880 subjects (see Table 1 below). All calculations were reviewed by 2 statisticians who will be involved in subsequent analyses.

Table 1: Sample size calculation adjusted for testing the hypothesis twice

| Least Meaningful Difference | 2006 rates  | Adjustment for use of bed-net | Rate unexposed | Rate exposed | Person-years | Follow-up years | n          | Loss to follow-up | Sample size per group* |
|-----------------------------|-------------|-------------------------------|----------------|--------------|--------------|-----------------|------------|-------------------|------------------------|
| 0.05                        | 3.44        | 0.75                          | 2.58           | 2.71         | 3017         | 0.42            | 7240       | 0.15              | 8326                   |
| 0.1                         | 3.44        | 0.75                          | 2.58           | 2.84         | 772          | 0.42            | 1854       | 0.15              | 2132                   |

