##### Secondary analysis

Univariate Poisson regression with the same outcome will be used to evaluate associations with other variables: iron status at baseline, breast-feeding, age, gender and use of bed-net. These will then be introduced and re-evaluated in a multiple Poisson regression model, which will allow for adjusted group comparisons. Most importantly, by including the baseline iron status variable and the interaction with the main group variable, we can focus on the iron sufficient children that are receiving iron supplements and compare them against the others. The Poisson models will be validated by checking the model fit and for over-dispersion. Adjustments or transformations will be used if necessary.

The number of hospital admissions will be analyzed in a similar fashion, using Poisson regression. The parasite count outcome will be compared between the two groups, using a t-test. Univariate associations with other factors will be verified here as well, using t-tests, correlation coefficients and univariate regression.

Ultimately a multiple regression model will be developed, again for the purpose of adjusted comparisons between groups.

The normality of the data will be verified and, in the case of any departures, a log-transformation will be used and the data reanalyzed. If the log-transformation fails to achieve normality, a nonparametric alternative will be used instead. All statistical analyses will be carried out using SAS 9.1. The Analysis will be carried out on an intention-to-treat basis including all randomized children.

Upon the completion of the first intervention phase, an interim analysis will be performed by a Data and Safety Monitoring Committee (DSMC) as described above (primary analysis). The study will be stopped if the incidence of malaria is higher in one group.

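### The sample size is built on about 2.5% two-sided per test for two tests, but section 5.5 uses a 95% interval at both, so the overall two-sided error is 8.3% to 9.75% rather than 5%

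*Protocol*

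**What the plan says.** Protocol 5.1, Sample Size, starts from the rate for which "the baseline rate of 3.44 episodes/child/year was assumed", reduced by the bed-net factor of 0.75 to 2.58. It continues: "We estimated that a total of 351 person-years would be required to detect a 15% increase in malaria incidence rates". For that figure the text gives a power of 80% and a type I error of 5%. The same paragraph says that the final number allows for "the need to test the hypothesis twice (due to the interim analysis by the Data Safety and Monitoring committee", and the table is headed "Table 1: Sample size calculation adjusted for testing the hypothesis twice". No per-test level is printed. The text calls the 351 a total, but Table 1 converts it directly to 843 and then 970 children per group, so it is a per-group figure.

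Protocol 5.5, Primary analysis, fixes the interval: "A 95% confidence interval for the ratio between the incidence in the iron group and the incidence in the placebo group will be calculated". Its upper limit is compared with a 10% tolerance limit to conclude non-inferiority. The end of 5.5 (under Secondary analysis) adds that after the first phase "an interim analysis will be performed by a Data and Safety Monitoring Committee (DSMC) as described above (primary analysis" and that the study stops if malaria incidence is higher in one group. No adjusted level is given for either analysis.

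**The concern.** The design allows for two tests and the analysis then ignores that allowance. This is not detail left for a later document: section 5.5 names a specific interval, and it does not fit the level on which the sample size rests. Two things are at stake. First, an overall 5% cannot be kept when each of two tests is run at 5%, and one of these tests can end the trial. Second, the protocol buys about 21% more person-time (351 against 291) for error control that the stated analysis does not deliver. Section 5.1 also contemplates a policy that differs by season, so a chance finding in either phase could influence practice.

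**Working it through.** **Inputs.** From 5.1 and Table 1: control rate λ0 = 3.44 × 0.75 = 2.58 per child-year; exposed rate λ1 = 2.58 × (1 + d); power 80%; follow-up 5/12 year (shown as 0.42); 15% loss. From 5.5: a 95% interval at each analysis and a margin of 1.10.

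**1. Reproducing Table 1.** For two Poisson rates, person-years per group = (z_α + z_β)² (λ0 + λ1) / (λ1 − λ0)². For d = 0.15, λ1 = 2.967, the sum is 5.547 and the difference is 0.387.

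- Two-sided 5%: (1.960 + 0.842)² × 5.547 / 0.387² = 7.849 × 5.547 / 0.1498 = 290.7
- Two-sided 2.5%: (2.241 + 0.842)² × 5.547 / 0.387² = 9.505 × 5.547 / 0.1498 = 352.0

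| Increase | Stated | At 5% | At 2.5% |
|---|---|---|---|
| 5% | 3017 | 2494.6 | 3021.0 |
| 10% | 772 | 638.9 | 773.7 |
| 15% | 351 | 290.7 | 352.0 |
| 20% | 202 | 167.3 | 202.6 |

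Solving each row for its level gives 0.0251 to 0.0253 two-sided, which fits either 5%/2 or 1 − √0.95 = 0.0253. A one-sided 5% level gives 229.0 in the 15% row and does not fit. Log-rate and square-root versions of the formula agree within 1 person-year in that row. The exposed rate must be left unrounded; with 2.97 the figures are 286.4 and 346.8, which leads to the same conclusion.

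**2. Where the adjustment sits.** 351 × 12/5 = 842 and 842.4 × 1.15 = 969, against 843 and 970 in the table. The allowance for two tests is therefore already inside the 351. At 5% per test the same steps give 290.7 × 12/5 = 698 and × 1.15 = 802 per group.

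**3. Overall two-sided error, taking the interval as the criterion at both tests.** The protocol does not say whether the final analysis pools the cohorts, so both cases are shown.

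- Seasons tested separately (independent): 1 − 0.95² = 9.75%. With 97.5% intervals: 1 − 0.975² = 4.9%.
- Pooled final, interim at half the information (bivariate normal, correlation √0.5 = 0.707): 8.3%. With 97.5% intervals: 4.3%.
- Pooled final, interim information fraction from 0.6 down to 0.3: 8.0% to 8.9%.

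**4. Harm direction only (iron above placebo).** Each 95% interval carries 2.5% in this tail. Over two tests: 4.2% pooled, and 1 − 0.975² = 4.9% separate. With 97.5% intervals: 2.1%, and 1 − 0.9875² = 2.5%.

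**5. False non-inferiority at a true ratio of 1.10.** Judged once, at the end: at most 2.5%, because an interim stop can only remove chances to make the claim. Claimable at either test: 4.2% to 4.9%.

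**6. Power.** For a 15% increase at 351 person-years per group, the standard error of the rate difference is √(5.547/351) = 0.1257 and 0.387/0.1257 = 3.078. Power is Φ(3.078 − 1.960) = 86.8% with a 95% interval and Φ(3.078 − 2.241) = 79.9% with a 97.5% interval. For non-inferiority at a true ratio of 1, the standard error of the log ratio is √(2/(2.58 × 351)) = 0.0470 and ln 1.10/0.0470 = 2.028. Power is 52.7% with a 95% interval and 41.6% with a 97.5% interval. Pooling both seasons (702 person-years per group) gives 2.868, hence 81.8% and 73.5%.

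**The case against.** Four points on the other side deserve weight.

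*The 5% in 5.1 may be the overall level.* The same paragraph goes on to allow for testing twice. Read that way, text and table agree, and a reader should not infer that the 5% is an error. This stands. It leaves the conflict in the 95% interval of 5.5, and the per-test level is still printed nowhere.

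*False claims of harm do not exceed 5%.* A reader might take 8.3% to 9.75% as the chance of wrongly concluding that iron raises malaria. About half of that figure is the opposite error, and the hypothesis in 5.1 is directional. The harm tail is 4.2% to 4.9%. This stands; the right comparison is with the 2.1% to 2.5% that the Table 1 level would give.

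*Non-inferiority need not be affected.* A reader might infer that its error doubles in any case. The interim is given one consequence, stopping for a higher incidence, and section 5.8(b) likewise speaks only of worse results on iron. No text ends the trial early on a non-inferiority claim. The doubling therefore holds only if either test may support that claim.

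*The interim criterion is not clear, and other documents may set it.* The stopping sentence in 5.5 has no significance threshold, and section 8.5 promises a detailed monitoring plan before accrual. So the error figures rest on an assumption about the criterion. This does not remove the point: 5.5 itself refers the interim to the primary analysis and hence to the 95% interval, and it fixes the same interval at the end.

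**Conclusion.** The point holds as a conflict between the level on which the trial is sized and the level at which it is to be analysed. That Table 1 rests on about 2.5% two-sided per test is firm, since all four rows agree. The excess in overall two-sided error, 8.3% to 9.75% instead of 5%, assumes that the 95% interval decides at both tests; the lower figure further assumes a pooled final analysis with half the information at the interim. The protocol does not support the stronger readings that false harm claims exceed 5%, that non-inferiority error is inflated whatever the claim rule, or that the 5% in 5.1 is necessarily mistaken. The conflict should be settled before unblinded Phase I data are seen.

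**What to change.** 1. **5.5, difference test.** Use a two-sided 97.5% interval at the interim and at the final analysis, or another pre-stated split totalling 5%. For a pooled final, a common critical value of 2.178 (about a 97.1% interval) gives 5.0% overall; 97.5% is slightly conservative there (4.3%) but is the level Table 1 already pays for. State whether the final analysis pools the cohorts.
2. **5.5, non-inferiority.** If either test may support the claim, apply the wider interval to the 10% limit as well. Otherwise state that non-inferiority is judged once, at the end, with a 95% interval.
3. **5.1.** State that 5% is the overall level, with two-sided 2.5% per test, 80% power and 351 person-years per group per season.
4. **Interim wording.** Reconcile three passages: the stopping sentence in 5.5, which has no threshold; the unblinding rule in 5.2, which depends on a significant difference; and 5.8(b), where the committee may recommend termination.

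No additional children are needed. The cost is intervals about 14% wider (2.241/1.960) and power for a 15% increase at each test of 79.9% instead of 86.8%. That includes the Phase I safety look, so the loss should be stated openly, although 80% is what the design promised. If the wider interval is also used for non-inferiority, power at a true ratio of 1 falls from 53% to 42% per season, or from 82% to 73% pooled.

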## 5. RESEARCH DESIGN AND METHODS

### 5.1 Design Conceptual or Clinical Framework

#### *Study Design*

The proposed study is a community-based blinded randomized controlled trial with 2 study arms that will be conducted in two phases:

- Phase I will take place during the dry season (December to April), when malaria transmission rates are lower. Eligible subjects (one per household) will be individually randomized to receive a daily dose of either a powdered vitamin/mineral fortificant containing 12.5 mg of iron (plus ascorbic acid, vitamin A and zinc), or a placebo (containing all micronutrients excluding iron), added to complementary foods, for 5 months.
- Phase II will take place during the wet season (June to October), when malaria transmission rates are higher. Eligible subjects, who did not participate in Phase I, will be individually randomized to one of the two study arms as described above and followed for 5 months.

A dual phase design, with two unique cohorts, was chosen so that preliminary results (at the end of phase 1) could be assessed by an independent Data Safety and Monitoring Committee. It is possible that during the dry season no impact of iron will be detected, while during the wet season, an impact will be observed. With this possible outcome, it is potentially feasible to translate this knowledge into a Ministry of Health Program to only provide iron supplementation (fortification) during the dry months of the year (December to April).

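### The sample size is justified for detecting a 15% increase in malaria, but the primary analysis concludes non-inferiority at a 10% limit, and the protocol gives no power for that test

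*Protocol*

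**What the plan says.** The sample size text in section 5.1 sets out a hypothesis of harm: "We hypothesize that the incidence of malaria will be significantly higher in children receiving iron versus a placebo of micronutrients without iron". The size is chosen to "detect a 15% increase in malaria incidence rates with 80% power and at a 5% type I error", and "a difference of 15% in malaria incidence was considered to be clinically significant". On the event rate, "the baseline rate of 3.44 episodes/child/year was assumed"; Table 1 multiplies this by 0.75 for bed-net use to reach 2.58. The table is titled "Sample size calculation adjusted for testing the hypothesis twice", and its selected 15% row reads 2.58 against 2.97 episodes per year, 351 person-years, n = 843, and 970 per group after losses. Each season has its own cohort of 1940 children.

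Section 5.5, under the primary analysis, compares incidence by Poisson regression with a 95% confidence interval for the iron-to-placebo ratio. Then: "The upper boundary of this confidence interval will be compared to the 10% tolerance limit". If the limit is lower, non-inferiority is concluded. Neither section gives a power or sample size for that rule. Section 5.5 also has the monitoring committee apply the primary analysis to Phase I alone at the interim.

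**The concern.** A power statement belongs to one hypothesis, one threshold and one error rate. Here the sizing asks whether iron raises malaria by 15%, while the decision rule asks whether an excess of 10% or more can be excluded. Good power for the first does not carry over to the second.

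The non-inferiority conclusion matters most for policy. Sections 2 and 3.3 tie a possible scale-up recommendation to showing that the powder does not raise malaria incidence, and failing to detect a 15% increase does not show that. If the 10% test has little power, a harmless product could well end with a result that shows neither harm nor non-inferiority. A reader who takes the 80% as the chance of a clear safety answer would be misled.

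**Working it through.** **Inputs.** Rate without iron 3.44 × 0.75 = 2.58 per child-year, and 351 person-years per group (Table 1). Follow-up: "randomized to one of the two study arms as described above and followed for 5 months", i.e. 5/12 = 0.42 years. Limit 1.10 and 95% interval (section 5.5). A true ratio of 1 is an assumption, because the protocol gives no expected ratio for this test.

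**Reproducing the plan's figure.** For two Poisson rates, person-years per group = (z₁₋α/₂ + z₀.₈₀)² (λ₀ + λ₁)/(λ₁ − λ₀)², with λ₀ = 2.58 and λ₁ = 2.58 × 1.15 = 2.967.
- Two-sided α = 0.025: (2.2414 + 0.8416)² × 5.547/0.387² = 352, against the stated 351. The other rows also match (3021, 774 and 203, against 3017, 772 and 202).
- Two-sided α = 0.05 gives 291 and one-sided 0.05 gives 229. Neither matches.
- 351/(5/12) = 842 (stated 843), and 843 × 1.15 = 969 (stated 970). So 351 is per group.

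Table 1 is therefore a difference test, with 5% apparently halved for two tests.

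**Power of the 10% test.** SE(log ratio) = √(2/(2.58 × 351)) = 0.0470. Power = Φ(ln 1.10/SE − z), with ln 1.10 = 0.0953, z = 1.96 for a 95% interval and z = 2.2414 if alpha is halved.

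| Unit of test | Person-years per group | SE | 95% interval | Alpha halved |
|---|---|---|---|---|
| One season | 351 | 0.0470 | Φ(0.068) = 53% | Φ(−0.213) = 42% |
| Both cohorts | 702 | 0.0332 | Φ(0.908) = 82% | Φ(0.627) = 74% |

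Per season, the upper limit falls below 1.10 only if the observed ratio is below 1.10/exp(1.96 × 0.0470) = 1.003. With a true ratio of 1, about 100 − 53 − 2.5 = 45% of single-season results would show neither harm nor non-inferiority.

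**Sensitivity (per season, 95% interval).**
- True ratio 1.05: 17%. True ratio 0.95: 87%. The SE is then √(1/(2.58 × 351) + 1/(2.58 × 351 × ratio)), and the log of the true ratio is subtracted from ln 1.10.
- Variance 1.5 times Poisson: 38%.
- Section 4 (KHRC Priority Research Areas) reports 7 attacks per child per year locally in under-fives. With the same bed-net factor, 7 × 0.75 = 5.25; SE = √(2/(5.25 × 351)) = 0.0329; power = Φ(0.933) = 82%, or about 66% with variance 1.5 times Poisson.

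**Size for 80% power at 1.10 per season, rate 2.58.** (1.96 + 0.8416)² × 2/(2.58 × 0.0953²) ≈ 670 person-years per group, against 351.

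**Power of the harm comparison.** At 351 person-years, 0.387/√(5.547/351) = 3.08. Power is 80% at two-sided 0.025 and Φ(3.08 − 1.96) = 87% at two-sided 0.05.

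**The case against.** Several stronger readings are tempting, and the protocol does not support them.

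- **That power is simply 53%.** Section 5.5 does not say the 10% test is done by season. Section 5.1 attributes testing twice to the interim analysis, which fits one interim and one final look. The timetable in 5.9 compiles data from both phases before a single analysis step. Over both cohorts the figure is 82%. Against that, each cohort is sized separately, the study design wants season-specific conclusions, and the interim applies the primary analysis to Phase I alone. Both readings are open.
- **That the event rate is fixed at 2.58.** The protocol's own local figure would put per-season power near 82% before over-dispersion. This stands as a range. But 2.58 is the rate the protocol planned on, and the study design expects lower transmission in the dry season.
- **That 10% was never considered.** Table 1 has a 10% row (772 person-years, 2132 per group). It is a difference-detection row and was not selected.
- **That the 80% describes no real use of the data.** The lower limit of the same interval tests for harm, and stopping after Phase I turns on higher malaria. The 80% covers that comparison.
- **That 10% and 15% contradict each other.** A difference to detect and a tolerance margin are different quantities, and a stricter margin is cautious. What stands is that the protocol does not explain how the two relate: a true 12% excess would exceed the tolerance yet fall short of the difference called clinically significant.

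An unseen SAP might name the unit of the test. The hypothesis, the sizing and the decision rule are all stated in the protocol, though, and they do not match there.

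**Conclusion.** The point holds as a mismatch between the sample-size justification and the primary decision rule. The 80% applies to detecting a 15% increase. The protocol gives no power for concluding non-inferiority at 10%.

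At the planning rate, with a true ratio of 1 and Poisson variance, that power is about 53% per season or 82% over both cohorts (42% or 74% with halved alpha). It moves strongly with the true ratio and the event rate, and over-dispersion lowers it. A reader might infer that the trial is bound to be underpowered for its safety claim. The protocol does not establish this, because it leaves the unit of the test open and contains a higher local rate. A higher rate would not remove the mismatch between hypotheses or explain the two thresholds.

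**What to change.** - State one primary hypothesis and use it in both 5.1 and 5.5. If detecting harm and concluding non-inferiority are both intended, say so and give each its own power.
- State whether the 10% test is done per season or season-stratified over both cohorts. This is a real trade-off: the combined test has more power, but it could mask the dry/wet contrast that the two-cohort design is meant to show.
- Replace or supplement the sentence on 80% power to detect 15% with the power of the 10% test under that choice, naming the assumed rate, true ratio and alpha, with a range for the rate and an allowance for over-dispersion.
- Explain how the 10% tolerance limit relates to the 15% difference called clinically significant.

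The cost is protocol wording and no extra children. The downside is that the stated power may be less favourable: per season at the planning rate, 53% or 42% in place of 80%.
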